### Sample size and power

Sample size calculation for this study is based on an expected difference of 7% in the proportions of patients not requiring interventions after 7 years between patients undergoing yearly standardised imaging surveillance (75% intervention-free rate^18^) versus those s not undergoing standardised imaging surveillance(82% intervention-free rate^19^). To detect this difference with 90% power and a 0.05 significance level, 719 patients per group are required and 1438 in total. To correct for the fact that the first CTA of approximately 20% of patients is abnormal, 1798 patients (1438/0.8) are needed.^20 21^ In addition, we expect incomplete data in 10% of the patients which results in a total number of 1997 patients (1798/0.9). With this sample size, we can also detect a 3% difference in aneurysm-related mortality with statistical significance. We chose a one-sided significance level (non-inferiority) of 0.05 and for standard proportion a 95% non-aneurysm-related mortality and thus 5% freedom from aneurysm-related mortality after 7 years: 0.95. For equivalence limit difference, we chose an acceptable difference between groups of 3%, in which if differences in aneurysm-related mortality equals 3%, they are considered non-inferior. Test-expected proportion is then equal to the standard proportion 0.97. Thus, the expected difference is 0, calculated with a power of 80%. This results in 653 patients per group and 1306 patients in total. Since the first CTA of approximately 20% of patients is abnormal, 1632 patients (1306/0.8) are needed. In addition, we expect incomplete data in 10% of the patients which results in a minimum of, 1813 patients (1632/0.9) are needed in total.

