### Statistical methods

Differences in baseline characteristics between patients undergoing or not undergoing yearly standardised imaging surveillance by either CTA or DUS, will be analysed using the χ^2^ or Fisher's exact test for categorical variables and the student's t-test or Mann-Whitney test for continuous variables, if appropriate.

The primary endpoints, that is, survival and freedom from intervention will be estimated by Kaplan-Meier survival analysis and differences between groups will be assessed with the log-rank test.

Secondary endpoints such as freedom from aneurysm rupture between patients with and without yearly standardised imaging surveillance will be estimated by Kaplan-Meier survival analysis, and differences between these groups will be calculated with the log-rank test.

Multivariable cox regression analysis will be used to determine survival and the freedom of intervention corrected for age, gender, AAA diameter, ASA classification, neck length, neck angulation and type of endograft. The association between postoperative intervention and the following covariates will be investigated with the multivariate Cox-regression analysis:

Age.Gender.AAA diameter.ASA classification.Neck length (>15 mm).Neck angulation (>60°).Type of endograft.Initial postoperative CTA.

All statistical analyses will be done with SPSS software (IBM, V.25). The level for statistical significance is set at a p value <0.05. The proportion of missing data will be displayed. The missing values will be imputed by multiple imputation techniques if this does not exceed 10%–15% and conduct a sensitivity analysis to investigate the effect of the missing data on the results of the analysis. If missing data on outcome variables exceeds 15%, we plan to perform subgroup analysis.

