Our study is subject to limitations due to the nature of administrative data and its retrospective and observational design. As with all studies using administrative data, it allows only the collection of data that was documented in patient medical records. It is also possible that some patients may have transferred to alternative surveillance protocols in different medical centres without our knowledge. The study will assess results in 17 medical centres over 11 years, during which time improvements in endograft and in clinical practice has occurred. Attrition bias due to loss to follow-up represents a threat to the internal validity of our cohort study. The mentioned e-survey has only been sent to participating vascular surgeons, perhaps surgeons participating in the ODYSSEUS study strongly believe that imaging surveillance frequency can be reduced. This may have provided a biased view of post-EVAR follow-up in the Netherlands. However, most of the high-volume EVAR centres in the Netherlands have been included. Another limitation is that no information is retrieved from patients’ medical records about when not to intervene and what the reason was for this decision.

In conclusion, with the ODYSSEUS study we aim to confirm the follow-up protocol of the recent ESVS guideline delaying imaging after 5 years if classified in the low risk group and therefore aim to investigate the intervention-free-survival and aneurysm-related mortality for patients with and without yearly imaging surveillance.

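### The missing-data rule is tied to a percentage: imputation stops above a vague 10%–15%, outcomes go to an undefined subgroup analysis, and incomplete covariates get no method

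*Protocol article*

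**What the plan says.** All of this is in the Protocol article.

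- **Statistical methods, first tier:** "The missing values will be imputed by multiple imputation techniques if this does not exceed" 10%–15%. The same sentence adds that the team will "conduct a sensitivity analysis to investigate the effect of the missing data on the results of the analysis". The proportion of missing data will also be displayed.
- **Statistical methods, second tier:** "If missing data on outcome variables exceeds 15%, we plan to perform subgroup analysis".
- **Statistical methods, models:** Kaplan-Meier with log-rank tests for the primary endpoints, and Cox models adjusted for age, gender, AAA diameter, ASA class, neck length, neck angulation and endograft type.
- **Sample size and power:** "we expect incomplete data in 10% of the patients".
- **Study procedures:** rupture dates come from hospital records, and date of death is verified against the municipal personal records database. The surveillance groups are defined by imaging at least every 16 months.
- **Discussion:** "Attrition bias due to loss to follow-up represents a threat to the internal validity of our cohort study".

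**The concern.** The article states a rule here; it does not merely leave detail to an analysis plan. The rule has four weaknesses.

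1. **The cut-off is a range.** At 12% missing, the text does not say whether imputation applies. It also does not say whether the percentage is counted per variable or per patient. The plan expects 10% of patients to be incomplete, which is the lower edge of the range, so the choice could end up being made after the data are seen.
2. **The trigger is the wrong quantity.** Multiple imputation can be sound at 30% missing and unsound at 5%. What matters is whether the observed variables explain the missingness and whether the imputation model is adequate.
3. **The outcome fallback does not address missing data.** A subgroup analysis changes who is studied. It does not account for outcomes that were not seen, and neither the subgroup nor the quantity to be estimated is given.
4. **Covariates are left without a method.** The second tier names outcome variables only. A covariate above the cut-off is no longer imputed and nothing replaces imputation. A Cox regression cannot use a record with a missing covariate, so those patients drop out unless another method is added.

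What is at stake is precision in the adjusted models and, under one reading of the subgroup, the fairness of the comparison between patients with and without yearly imaging. Patients seen less often may have thinner hospital records on interventions and ruptures. Restricting the analysis to well-documented patients could then select on the exposure.

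**Working it through.** **The plan's own figures.** Inputs from Sample size and power: intervention-free rates of 75% and 82%, 90% power, 0.05 significance (two-sided reproduces the result), 20% abnormal first CTA, 10% incomplete data.

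- n per group = (1.960 + 1.2816)² × (0.75×0.25 + 0.82×0.18) / 0.07² = 10.508 × 0.3351 / 0.0049 = 718.6, so 719 per group and 1438 in total, as stated.
- 1438 / 0.8 = 1797.5 (stated as 1798), and 1798 / 0.9 = 1997.8 (stated as 1997).

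So 1438 is already net of the 10% allowance. The right base for further losses is the number with a normal first CTA: 1997 × 0.8 = 1597.6, about 1598.

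**Covariates above the cut-off.** Assumption, not in the documents: neck length and neck angulation are each missing in 20%, and nothing else is missing. Standard errors are taken as proportional to 1/√n, with the group split and event proportion unchanged.

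| Overlap of missingness | Patients kept | SE relative to 1438 |
|---|---|---|
| Independent | 1597.6 × 0.8² = 1022 | √(1438/1022) = 1.19 |
| Complete overlap | 1597.6 × 0.8 = 1278 | √(1438/1278) = 1.06 |

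At 30% each, the counts are 1597.6 × 0.49 = 783 (SE ratio 1.36) and 1597.6 × 0.70 = 1118 (SE ratio 1.13). Both neck measurements may well be missing together, so the truth probably lies between the two rows.

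**Outcomes above the cut-off, if only observed cases are analysed.** Assumptions: 1997 enrolled, equal groups, n per group = 1997 × 0.8 × (1 − m) / 2, and the plan's 75% against 82%.

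| Missing m | n per group | Power |
|---|---|---|
| 10% | 719 | 90% |
| 15% | 679 | 88% |
| 20% | 639 | 86% |
| 30% | 559 | 81% |

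The loss of power is moderate.

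**Does 15% mark a change in validity?** This was checked with a simulation whose mechanism is assumed: 1598 patients, a binary outcome, one observed covariate that predicts the outcome, and missingness that depends on that covariate and on group.

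| Missing | Full-data difference | Observed cases only | Multiple imputation |
|---|---|---|---|
| 6% | −0.075 | −0.085 | −0.075 |
| 12% | −0.075 | −0.092 | −0.076 |
| 16% | −0.073 | −0.095 | −0.074 |
| 21% | −0.074 | −0.100 | −0.075 |
| 30% | −0.072 | −0.105 | −0.071 |

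The distortion in the unadjusted observed-case estimate grows smoothly from about 0.01 to about 0.03, and nothing changes at 15%. The imputation model was correct by construction, so this shows only that the percentage is not the deciding factor. It does not estimate the bias in this study.

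**The case against.** The strongest points on the other side are these.

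- **Safeguards exist.** Missingness will be reported, a sensitivity analysis is planned, and the Discussion acknowledges attrition. This stands, although the sensitivity analysis is written into the sentence on the imputation tier, so it is not clear that it applies above the cut-off.
- **The trigger may never be reached.** The plan expects 10% incomplete. This stands as a reason to call the problem contingent. It does not settle what happens between 10% and 15%.
- **Bias is not shown.** A reader might infer that the most incomplete variables receive the most biased handling. The documents do not support that. The subgroup rule covers outcomes only, and reading the subgroup as complete cases is an inference. A covariate-adjusted Cox model can be unbiased without imputation if its covariates explain the missingness. If missingness depends on unobserved values, imputation can be biased too.
- **Attendance does not explain everything.** Neck anatomy, diameter and ASA class are baseline data, so their absence does not follow from later non-attendance. Vital status is checked against the municipal database. The link to surveillance is plausible mainly for interventions and ruptures.

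Two further inferences should be set aside. The plan nowhere says that event times will be imputed; Kaplan-Meier and Cox methods already use censoring, and an article may leave the censoring dates to a fuller document. The 10% allowance in the sample size does not conflict with imputation either. It is simply conservative, because imputation does not restore all the lost information.

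**Conclusion.** The concern holds in a limited form. The plan fixes a missing-data rule whose cut-off is vague and has no statistical basis, whose outcome fallback is undefined and is not a missing-data method, and which leaves covariates above the cut-off with no method at all.

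Under the assumed 20% missingness in each neck measurement, default deletion would make standard errors about 6% to 19% larger than planned. If 20% to 30% of outcomes were missing and only observed cases were used, power would be about 86% to 81%. These losses are moderate and rest on missingness rates that the documents do not give.

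The more serious possibility is selection related to surveillance status, for interventions and ruptures taken from hospital records and less so for death. It arises only if the subgroup means patients with complete records, and its size and direction are unknown. The rule does not invalidate the study, but it is cheap to correct before analysis.

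**What to change.** - Delete the 10%–15% trigger and the subgroup rule.
- Multiply impute incomplete Cox covariates. The imputation model should include surveillance status, the other covariates, the event indicator and the cumulative hazard.
- State that incomplete follow-up for intervention and rupture is analysed by censoring at last documented contact.
- Report two sensitivity analyses at any level of missingness: a complete-case analysis, and a scenario in which outcomes are worse after loss to follow-up.

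The cost is a change of wording and modest extra programming, with no new data. The main downside is reliance on a missing-at-random assumption for the covariates and on non-informative censoring for the events. The sensitivity analyses are there to probe both.

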## Discussion

The goal of this study is to evaluate whether a reduction in follow-up visits and imaging and thus costs, in patients operated on for an asymptomatic or symptomatic AAA with EVAR is safe. We hypothesise that there will be less interventions and no difference in aneurysm-related mortality in patients with less intensive follow-up. With the results of this study, we aim to provide scientific evidence helping vascular surgeons decide whether less vigilant follow-up after EVAR may be considered for patients classified in the low risk group.

The strengths of the ODYSSEUS study are that it can accumulate the data of a large number of consecutive EVAR patients with a theoretical follow-up of 6 to 11 years, and that it captures all surveillance visits, long-term outcomes and mortality post-EVAR. Moreover, 17 medical centres throughout the Netherlands are participating in this study, including university and general hospitals, thereby reducing selection bias.

An e-survey has been sent to all vascular surgeons participating in the ODYSSEUS study. This shows that yearly imaging surveillance is upheld by most vascular surgeons in the Netherlands. In addition, most physicians agree that yearly imaging frequency can be safely reduced in a specific group of EVAR patients. As support for this reduction in frequency is evident in the Netherlands, the next step will be to study the groups for which it will be safe to deviate from the widely accepted surveillance protocols.

Our study is subject to limitations due to the nature of administrative data and its retrospective and observational design. As with all studies using administrative data, it allows only the collection of data that was documented in patient medical records. It is also possible that some patients may have transferred to alternative surveillance protocols in different medical centres without our knowledge. The study will assess results in 17 medical centres over 11 years, during which time improvements in endograft and in clinical practice has occurred. Attrition bias due to loss to follow-up represents a threat to the internal validity of our cohort study. The mentioned e-survey has only been sent to participating vascular surgeons, perhaps surgeons participating in the ODYSSEUS study strongly believe that imaging surveillance frequency can be reduced. This may have provided a biased view of post-EVAR follow-up in the Netherlands. However, most of the high-volume EVAR centres in the Netherlands have been included. Another limitation is that no information is retrieved from patients’ medical records about when not to intervene and what the reason was for this decision.

In conclusion, with the ODYSSEUS study we aim to confirm the follow-up protocol of the recent ESVS guideline delaying imaging after 5 years if classified in the low risk group and therefore aim to investigate the intervention-free-survival and aneurysm-related mortality for patients with and without yearly imaging surveillance.

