### General study design

A multicentre retrospective cohort study in 17 medical centres in the Netherlands. Data will be collected from the medical records of all consecutive patients with AAA who underwent EVAR between January 2007 and January 2012. This selection provides a theoretical length of follow-up of 6–11 years on December 2018. Patients will be divided into three groups: (A) patients without abnormalities at their first postoperative CTA with yearly imaging surveillance, (B) patients without abnormalities at their first postoperative CTA without yearly imaging surveillance and (C) patients with abnormalities at their first postoperative CTA (figure 1). This retrospective design has the advantage of collecting long term follow-up data. The Dutch Dream trial found that the number of interventions starts to rise 4 years after EVAR and the long-term results of the EVAR-1 trial show that EVAR has an early survival benefit but inferior late survival compared to open surgical repair.^13 14^ This is in contrast to the recently published long-term results of the OVER trial in which no difference was observed between EVAR and OSR in the primary outcome of all-cause mortality.^15^ Hence, a prospective study would take approximately 8 to 10 years to gather enough patients with adequate follow-up.

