**Figure 1 F1:**
[figure not shown]
Patient subgroups. AAA, abdominal aortic aneurysm; CTA, CT angiography; EVAR, endovascular aneurysm repair.

The standard of care is defined by the current guidelines and IFU. The usual follow-up schedule in the IFU is: CTA and abdominal X-ray at 30 days, 6 and 12 months and yearly thereafter. The 2019 ESVS guidelines recommend a CTA 30 days after EVAR. If there is adequate seal and no endoleak, patients are classified as low risk and CTA follow-up may take place 5 years later. If there is an inadequate seal and endoleak type I/III patients could be either evaluated for re-intervention or if sac shrinkage occurs yearly DUS is recommended. In the 2018 SVS guideline, CTA at 1 and 12 months is recommended and if neither endoleak nor sac enlargement is documented, DUS is suggested for annual postoperative surveillance. In our study design, the definition of compliance is undergoing imaging surveillance every 16 months since patients in most centres will be rescheduled if they missed their annual follow-up visit. Device-specific complications after EVAR will also be examined.

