### Study procedures

The primary outcomes of this study are interventions and aneurysm-related mortality for patients who had a normal initial postoperative CTA and who do adhere to our definition of yearly imaging surveillance over a 6-year to 11-year follow-up period, compared to those who do not adhere to our definition.

Interventions are EVAR-related interventions defined by the SVS reporting standards as postoperative adjunctive manoeuvres.^16 17^ Interventions for wound complications at the access site are not included, since these are detectable without the use of imaging.

Date of death during follow-up, if applicable, will be obtained from patient medical records and verified by the Dutch municipal personal records database (GBA).

Details of all surveillance imaging are obtained from patient medical records and radiology reports. The time between imaging appointments is calculated to determine whether patients adhere to this studies definition of with yearly imaging surveillance, that is, within every 16 months.

Date, type, indication and outcome of all postoperative imaging during follow-up are obtained from patient medical records, specifically imaging order forms and radiology reports. A normal initial postoperative CT scan is defined as a CT scan which shows no endoleaks, endograft migration (>10 mm), kinking or obstruction. All imaging outcomes are based on the report compiled by radiologists. These reports will not be re-evaluated by an independent radiologist, since we want to base our outcomes on real life data.

Secondary outcomes are all-cause mortality, type I, type II, type III and type IV endoleak, graft or outflow (iliac) occlusion, aneurysm rupture and endograft infection. This is also obtained from patient medical records, specifically radiology reports and Dutch municipal personal records database (GBA).

Date of aneurysm rupture is obtained from patient medical records, specifically operative reports, radiology reports and progress notes.

Costs of all EVAR-related imaging and outpatient clinic visits will be calculated per patient. Cost is defined as volume times price. Prices from the ‘Cost manual of the Dutch Health Care Institute’’ will be used. Costs for the patients will also be included. The quality-adjusted life years, a generic measure of disease burden including both the quality and quantity of life, cannot be calculated with this retrospective design.

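### The stated aim of confirming a 5-year imaging delay in low-risk patients goes beyond a design that compares only yearly with not-yearly imaging

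*Protocol article*

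**What the plan says.** **The aim.** The last paragraph of the Discussion states "we aim to confirm the follow-up protocol of the recent ESVS guideline delaying imaging after 5 years if classified in the low risk group", and derives from it the comparison of patients with and without yearly imaging. Study objectives is softer: it asks whether imaging frequency could have been reduced safely in a selected group.

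**The exposure.** Under General study design, "the definition of compliance is undergoing imaging surveillance every 16 months". Study procedures adds how this is judged: "The time between imaging appointments is calculated to determine whether patients adhere to this studies definition of with yearly imaging surveillance". Group B is "patients without abnormalities at their first postoperative CTA without yearly imaging surveillance". No minimum gap and no 5-year subset is defined. Statistical methods analyses the two-way contrast of with versus without yearly imaging.

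**The population.** General study design summarises the guideline as follows: "If there is adequate seal and no endoleak, patients are classified as low risk and CTA follow-up may take place 5 years later". Study procedures gives the study's own rule: "A normal initial postoperative CT scan is defined as a CT scan which shows no endoleaks, endograft migration (>10 mm), kinking or obstruction". Seal is in the first definition and not in the second.

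**The concern.** The closing aim names a specific imaging interval (5 years) in a specific population (the guideline's low-risk class). The design fixes neither. Group B is defined by failing the 16-month rule, so it can hold patients with a single late scan alongside patients not imaged for many years. The normal-CTA group is selected on different criteria from the low-risk class.

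At stake is how a favourable result would be read. A finding of no excess aneurysm-related mortality in B could be reported as support for a 5-year imaging-free interval, although the plan gives no means of showing how much of B's follow-up was spent in such an interval. Separately, patients in B whose imaging hardly differs from A's would weaken the contrast on which both sample size calculations rest.

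**Working it through.** **1. Aim against design**

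| Element | Closing aim / guideline as summarised | Study as designed |
|---|---|---|
| Interval | CTA 5 years later | Any pattern that fails imaging every 16 months |
| Population | Adequate seal and no endoleak | No endoleak, migration over 10 mm, kinking or obstruction |
| Contrast analysed | Would need a 5-year group | A versus B only |

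The interval and the population both differ. The seal point is a mismatch of population: it affects A and B alike and does not dilute the contrast between them.

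**2. The plan's own sample sizes reproduce** (inputs from Sample size and power)

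- Interventions, 75% v 82% intervention-free, two-sided 0.05, 90% power, unpooled variance: n = (1.960 + 1.282)² × (0.75×0.25 + 0.82×0.18) / 0.07² = 718.6, so 719 per group, as stated.
- Aneurysm-related mortality, 95% in both groups, margin 0.03, one-sided 0.05, 80% power: n = (1.645 + 0.842)² × 2×0.95×0.05 / 0.03² = 652.6, so 653 per group, as stated. The same section also mentions 0.97, but 0.97 in both groups gives 400, so 0.95 is used below.

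The arithmetic is sound. The issue is what contrast it is applied to.

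**3. Effect of near-yearly imaging within B**

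Let f be the share of B that is in effect imaged yearly. The documents do not give f, so it is assumed over 0 to 0.75.

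*Mortality.* Suppose truly reduced imaging is worse by D. Then the proportion in B free from aneurysm-related death is p_B = 0.95 − (1−f)D, SE = √[0.95×0.05/653 + p_B(1−p_B)/653], and P(declare non-inferiority) = Φ{[0.03 − (1−f)D]/SE − 1.645}. Example with D = 0.03 and f = 0.5: p_B = 0.935, SE = 0.0129, Φ(0.015/0.0129 − 1.645) = Φ(−0.48) = 32%.

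| f | D = 3 points | D = 6 points |
|---|---|---|
| 0 | 5% | 0% |
| 0.25 | 14% | 0.4% |
| 0.50 | 32% | 5% |
| 0.75 | 56% | 32% |

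*Interventions.* With 719 per group and B's rate 0.75 + 0.07(1−f), power for the two-sided 0.05 test is:

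| f | Difference | Power |
|---|---|---|
| 0 | 7.0 points | 90% |
| 0.25 | 5.25 points | 67% |
| 0.50 | 3.5 points | 35% |

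**4. How many in B have a 5-year gap?**

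The documents do not say. As an illustration, assume 9 annual scans are due, the chance of a miss after an attended scan is 10%, and any miss puts the patient in B. Four misses in a row then give a 5-year gap. Enumerating all 2⁹ sequences:

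- P(B) = 1 − 0.9⁹ = 61%, whatever the clustering.
- The rest depends on the assumed chance of missing again after a miss:

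| Chance of missing again | Exactly one miss, within B | Four or more in a row, within B |
|---|---|---|
| 0.1 (independent) | 63% | 0.1% |
| 0.5 | 38% | 11% |
| 0.7 | 26% | 28% |
| 0.8 | 20% | 42% |

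The 5-year share runs from about 0.1% to 42% on assumptions that the documents cannot settle.

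**The case against.** The strongest defence is that the defect is one loosely worded sentence. The Abstract, Study objectives, the endpoint sections and the rest of the Discussion describe yearly versus not-yearly imaging, and no endpoint or sample size rests on a 5-year interval. That is fair, and it is why narrowing the wording is an acceptable remedy. But the sentence is the article's stated conclusion, and the plan followed exactly cannot deliver it.

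Four stronger readings are tempting and are not supported:

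- *One gap over 16 months puts a patient in B.* This is the literal meaning of the compliance rule, but the article does not say how many gaps count, and the operational rule may stand in a fuller document.
- *Almost no one in B had a 5-year gap.* That follows only if scans are missed independently. Non-attendance is likely to cluster, and the background section reports one centre already imaging every 5 years (when this began is not stated). Relevant patients may exist; they are just not separated.
- *The comparison is biased towards non-inferiority.* Dilution has that effect only for aneurysm-related mortality, and only if reduced imaging does harm. For interventions, where B is expected to do better, it works against the study's own hypothesis. Non-inferiority appears only in the sample size section, while Statistical methods plans log-rank tests of difference. In a non-randomised comparison, confounding can move the net bias either way.
- *Leaving out seal makes the study population simply looser.* The study adds migration, kinking and obstruction, which the guideline summary does not list, and attachment-site endoleaks are already excluded. The two populations differ, but the direction is not fixed.

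**Conclusion.** The point holds as a mismatch between the closing aim and the design. An A-versus-B result can inform on imaging that is not yearly, in patients with a normal first CTA by the study's definition. It cannot confirm a 5-year delay in the guideline's low-risk group.

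The mismatch itself needs no assumption. The cost of dilution does: with a quarter to a half of B in effect imaged yearly, the error rate for non-inferiority on mortality goes from 5% to about 14% to 32% when true harm equals the margin, and power for interventions drops from 90% to about 67% to 35%. These figures rest on an assumed share, the plan's own rates and a normal approximation. They show sensitivity and do not estimate what will happen. The share of B with a 5-year gap cannot be known from the documents.

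**What to change.** 1. Add an analysis by time-updated imaging-free interval (time since last scan), with person-years and events tabulated per category. Possible categories are up to 16, 16–24, 24–60 and over 60 months. The outer limits follow the study's 16-month rule and the guideline's 5 years; the inner cut is a choice to be fixed in advance.
2. Make a statement about a 5-year interval only from the longest category. If it is too thin, or if the analysis is not added, limit the aim and conclusion in the Discussion to not-yearly versus yearly imaging, in line with Study objectives.
3. State how many intervals over 16 months move a patient from A to B.
4. Describe the population as having a normal first CTA by the study definition, not as the guideline's low-risk group.

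The cost is one extra analysis, since the date of every postoperative scan is already collected, and possibly a narrower conclusion. No new data collection is needed.
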